## Methods and design

### Study design

This is a two-arm, double-center, randomized controlled trial. A total of 148 CSAP patients will be enrolled and randomly assigned to two groups through central randomization in a 1:1 ratio. This trial will include a 2-week screening period, a 4-week treatment period, and a 4-week follow-up period. Outcome assessments will be performed at the baseline, the end of treatment, and the end of follow-up (see Fig. 1 for the details of the study schedule).

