### Sample size

In this study, we assume that H0 represents the clinical effect of Group A is the same as Group B; H1 represents the effect of Group A is not the same as Group B.

According to the formula: $$ n=\frac{2{\sigma}^2}{{\left(\mu 1-\mu 2\right)}^2}\times {\left({\mu}_{\alpha /2}+{\mu}_{\beta}\right)}^2 $$ [23]. In this study, assuming α = 0.05 (both sides), 1-β = 0.80. Based on our previous study [12], *μ*1 is the improvement of the frequency of angina attacks in the acupoints on the disease-affected meridian group, and *μ*2 is the improvement of the frequency of angina attacks in the acupoints on the non-affected meridian group. With *μ*1 = 5.57 and *μ*2 = 3.14, σ is estimated to be 5, and the sample size is calculated as 67 per group. Considering a dropout rate of 10%, we concluded that the sample size is 73.6 per group, and each group needs 74 cases after taking an integer. Therefore, a total of 148 CSAP patients will be finally recruited.

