### Patient safety

To guarantee the safety of patients, acupuncture treatment will be performed in the cardiology department where cardiovascular specialists and first-line physicians can participate in emergency timely. All adverse events (AEs) such as pain, allergy, bleeding, hematoma, and fainting should be recorded in the case report form (CRF) carefully. Serious adverse events (SAE) such as death or life-threatening events should immediately be reported to the principal investigator.

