### Data analysis

All analyses will be strictly conducted according to the intention-to-treat (ITT) principle. Continuous variables will be described with means and standard deviation (SD) or median, maximum, minimum, P25, and P75. Categorical variables will be described with numbers and percentages (%).

For the frequency of angina attacks from baseline to 4 weeks after inclusion, if the distribution conforms to the approximately normal distribution, analysis of covariance (ANCOVA) will be used. Since this study is a multicenter clinical trial, the center effects will be included in the analysis model. Age, gender, duration of the disease, and study site will be included in the model as covariates. Considering clustering effects of the number of angina attacks per patient, a hierarchical Poisson regression will be conducted exploratively. Separate ANCOVA analyses will be performed for secondary outcomes. The incidence of AEs in both groups will be compared with a Poisson regression model in which the number of participants with AEs is an independent variable and the group is a dependent variable.

Missing data will be imputed by multiple imputation. A sensitivity analysis using a pattern-mixture model will be conducted to assess the robustness of the results.

For all statistical analyses, Statistical Analysis System version 9.4 software (SAS Institute Inc., Cary, North Carolina) will be used. A *P* value of less than 0.05 (*α* value of 0.05, two-sides) will be considered statistically significant.

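### The adverse-event Poisson model has its variable roles reversed, so its coefficient is not the between-group incidence ratio that it is meant to give

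*Protocol article*

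**What the plan says.** The protocol article deals with AE analysis in one sentence of the Data analysis section. Its first half gives the aim: "The incidence of AEs in both groups will be compared with a Poisson regression model". Its second half assigns the roles: "in which the number of participants with AEs is an independent variable and the group is a dependent variable".

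Nothing else in the article gives another AE model or corrects these roles. The Patient safety section concerns recording and reporting only: "All adverse events (AEs) such as pain, allergy, bleeding, hematoma, and fainting should be recorded in the case report form (CRF) carefully". No expected AE rate is given. Study design fixes the allocation: "A total of 148 CSAP patients will be enrolled and randomly assigned to two groups through central randomization in a 1:1 ratio". Sample size gives the number per arm: "each group needs 74 cases after taking an integer". The significance threshold for all analyses is a two-sided P "value of less than 0.05".

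**The concern.** The two halves of the sentence do not fit together. Comparing incidence between groups means modelling how often AEs occur, given group. The sentence instead makes group the outcome. Group is a two-level label set by 1:1 randomisation. It is neither a count nor an incidence, and its distribution is fixed by design.

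What is at stake is the effect measure for safety. If the sentence were followed, or if the output of such a model were labelled as an incidence ratio, the reported number would not answer the question asked. Readers comparing the tolerability of the two point prescriptions could be given a ratio that neither matches the AE percentages nor inverts when the groups are swapped.

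**Working it through.** **Inputs.** 74 patients per arm (Sample size). Two-sided 0.05 (Data analysis). The article states no AE figure, so there is nothing to reproduce; all AE counts below are assumptions, spread over a range. Let *a* and *b* be the patients with at least one AE in groups A and B, and *n* = 74.

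**Reading used.** The article's wording refers to a number of participants, which is an arm-level quantity. To obtain a reversed model that can be fitted, I used each patient's AE status (0/1) as the predictor and group (0/1) as the response, with a log link.

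**Formulas.**
- Correct orientation (AE as response, group as predictor): exp(β) = (*a*/*n*)/(*b*/*n*), the incidence ratio.
- Reversed, A coded 1: exp(β) = P(A | AE)/P(A | no AE) = [*a*/(*a*+*b*)] / [(*n*−*a*)/(2*n*−*a*−*b*)].
- Reversed, B coded 1: exp(β) = [*b*/(*a*+*b*)] / [(*n*−*b*)/(2*n*−*a*−*b*)], inverted below so that it is on the same A-to-B scale.

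**Worked case, 15 v 5.**
- Correct: (15/74)/(5/74) = 3.00.
- Reversed, A = 1: (15/20)/(59/128) = 0.750/0.461 = 1.63.
- Reversed, B = 1: (5/20)/(69/128) = 0.250/0.539 = 0.464; inverse 2.16.

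A genuine between-group ratio would invert exactly when the coding is switched. This one does not.

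**Range of assumed counts.**

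| AEs, A v B (of 74 each) | Incidence ratio | Reversed, A = 1 | Reversed, B = 1, inverted |
|---|---|---|---|
| 8 v 4 | 2.00 | 1.37 | 1.54 |
| 10 v 5 | 2.00 | 1.39 | 1.56 |
| 12 v 6 | 2.00 | 1.40 | 1.57 |
| 20 v 10 | 2.00 | 1.46 | 1.63 |
| 30 v 15 | 2.00 | 1.56 | 1.72 |
| 70 v 35 | 2.00 | 7.17 | 2.72 |
| 15 v 5 | 3.00 | 1.63 | 2.16 |

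In the first six rows the incidence ratio is held at 2.00, yet the reversed value moves with the AE frequency. It lies below 2.00 in the first five rows and above it at 70 v 35: (70/105)/(4/43) = 7.17. With no association (*a* = *b*) both orientations give 1, so the reversed model keeps some information on association but loses the intended scale.

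**p-values.** Poisson models fitted to the same data:

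| Counts | Variance | Correct | Reversed, A = 1 | Reversed, B = 1 |
|---|---|---|---|---|
| 15 v 5 | model-based | 0.033 | 0.092 | 0.097 |
| 15 v 5 | robust | 0.025 | 0.002 | 0.052 |
| 20 v 10 | model-based | 0.074 | 0.151 | 0.152 |
| 20 v 10 | robust | 0.048 | 0.021 | 0.073 |

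With model-based variance the reversal weakens the evidence in both cases. With robust variance it strengthens it when A is coded 1 and weakens it when B is. The direction of the error therefore cannot be stated without knowing the variance estimator and the coding, and the article gives neither.

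**The case against.** The best defence is that this is a transposition of two terms, not a plan that anyone would run. The same sentence names incidence as the target, the number of participants with AEs is a natural Poisson response, and an arm-level count cannot literally serve as a patient-level predictor. A competent analyst would probably swap the roles without comment. Categorical variables are also to be described with counts and percentages, so a reader should be able to work out the incidence ratio from the AE table. All of this stands, and it lowers the severity. It does not make the sentence right: the roles are stated explicitly, and nothing in the article overrides them.

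A reader might also infer more than the article supports:

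- *That a real safety difference will be understated.* Attenuation is usual at low to moderate AE rates, but 70 v 35 goes the other way, and with robust variance and A coded 1 the reversed p-value is smaller than the correct one.
- *That the model returns one particular wrong number.* The AE counts are assumed and the coding is not stated, so 1.63 and 2.16 are both illustrations.
- *That standard errors will be too wide because a yes/no outcome is given a Poisson variance.* The article does not say which variance will be used. That detail, like any exact test for sparse events, may properly sit in the full protocol or analysis plan, which is not shown.
- *That this is the trial's only safety comparison.* It is the only one in this condensed article; the full plan may contain others.

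**Conclusion.** The point holds as an error of specification: the stated model does not estimate the quantity that its own sentence sets out to compare. That conclusion needs no assumption about AE rates. The size does. At 74 per arm, with an incidence ratio of 2.00 and counts from 8 v 4 to 30 v 15, the reversed model gives 1.37 to 1.72 depending on frequency and coding. These figures rest on assumed counts and on reading the predictor as per-patient AE status.

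Severity is should-fix. A higher grade is not supported: the error is probably one of wording, it sits in a safety analysis, and the primary outcome, the sample size and the collection of AE data are unaffected.

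**What to change.** Replace the second half of the sentence so that AE occurrence is the dependent variable and group the independent variable. Either form will do:

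- per participant: at least one AE (yes/no) as the response in a log-link Poisson model, for which robust variance is suitable; or
- per arm: the number of participants with at least one AE as the response, with the log of the number of participants as offset.

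In both cases, state that the incidence ratio between groups will be reported with its 95% CI, and name the reference group.

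The cost is one sentence. No data item, visit, sample-size figure or aspect of conduct changes. The Trial status section reports 12 patients included at the time of writing, so the wording could be corrected well before any analysis. If the full analysis plan already has the roles the right way round, only the published sentence needs correcting.

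### The adverse-event regression is written with response and predictor swapped, so it does not estimate adverse-event incidence by group

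*Protocol article*

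**What the plan says.** The Data analysis section gives one between-group safety analysis. Its aim is clear: "The incidence of AEs in both groups will be compared with a Poisson regression model". The same sentence then assigns the roles in that model: "the number of participants with AEs is an independent variable and the group is a dependent variable". The Patient safety section says which events are collected ("All adverse events (AEs) such as pain, allergy, bleeding, hematoma, and fainting should be recorded") but adds nothing on how they are analysed. No other section restates or corrects the model. The Study design section fixes the structure of the comparison: two groups, 148 patients, allocated 1:1.

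**The concern.** The two halves of the sentence contradict each other. Comparing incidence between groups requires AE occurrence as the response and group as the predictor. The specification is the reverse, with a two-level randomised label treated as a Poisson count.

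In a logistic model of two binary variables the slip would matter less, because the unadjusted odds ratio is the same in either direction. A log-link Poisson model has no such symmetry. Its coefficient is a ratio of means of whatever stands on the left-hand side, here the numeric codes given to groups A and B. That is neither a risk ratio nor a rate ratio for AEs. An analyst following the text literally would report an uninterpretable effect and could miss a real difference in tolerability between the two prescriptions.

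**Working it through.** **Inputs.** From the article: two groups, 1:1, 74 per group (Study design; Sample size), and a two-sided 0.05 level (Data analysis). The article gives no AE rate and no figure for this model, so there is nothing of the plan's own to reproduce here. The AE counts are assumptions.

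**Worked example (assumed).** 30/74 with at least one AE in group A and 15/74 in group B. That makes 45 participants with an AE (30 A, 15 B) and 103 without (44 A, 59 B).

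**Correct orientation, AE on group.**
- Risk ratio = (30/74)/(15/74) = 2.00.
- Model-based SE of the log ratio = √(1/30 + 1/15) = 0.316.
- z = ln 2/0.316 = 2.19, P=0.028.
- Switching the reference group gives 0.50 with the same P.

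**As written, group on AE (yes/no per patient).** With a single binary predictor the fit is exact:
- exp(β) = (S₁/45)/(S₀/103), where S₁ and S₀ are the sums of the group codes among participants with and without an AE.
- Model-based SE of β = √(1/S₁ + 1/S₀).

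| Coding (A, B) | S₁ | S₀ | exp(β) | SE | z | P |
|---|---|---|---|---|---|---|
| 1, 0 | 30 | 44 | 1.56 | 0.237 | 1.88 | 0.060 |
| 0, 1 | 15 | 59 | 0.58 | 0.289 | −1.87 | 0.061 |
| 1, 2 | 60 | 162 | 0.85 | 0.151 | −1.09 | 0.27 |
| 2, 1 | 75 | 147 | 1.17 | 0.142 | 1.09 | 0.27 |

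No coding returns 2.00 or 0.50.

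**Other assumed counts.** For 15 v 7, 12 v 6 and 20 v 10 out of 74, the correct model gives 2.14, 2.00 and 2.00. Over these and the worked example, the swapped model gives 1.40–1.56 (coding 1, 0), 0.58–0.64 (0, 1), 0.85–0.88 (1, 2) and 1.13–1.17 (2, 1).

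**Robust standard errors do not remove the dependence on coding.** For 15 v 7 the correct model has robust P=0.074. The swapped model has robust P=0.031 with A=1, B=0 and 0.112 with A=0, B=1, on opposite sides of 0.05.

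**The literal aggregate reading.** If the predictor is the number of participants with AEs per group, there are two data points and two parameters.
- With codes 1 and 2 the slope is ln(1/2)/(30−15) and its SE is √(1/1 + 1/2)/(30−15). The counts cancel: |z| = ln 2/√1.5 = 0.566, P=0.57 for any two unequal AE counts.
- With codes 0 and 1 the fit needs the logarithm of zero, and no finite estimate exists.

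**Rejection rates.** Computed by summing over all binomial outcomes with 74 per group, two-sided 0.05, model-based Wald tests for the Poisson fits. The incidences are assumed.

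| Incidence | Pearson chi-square | Poisson, correct | Swapped, 0/1 | Swapped, 1/2 |
|---|---|---|---|---|
| 20% v 40% | 77% | 61.5% | 45% | 1% |
| 10% v 30% | 88% | 81% | 59–61% | 2% |
| 30% v 50% | 72% | 48% | 39% | 1% |
| 20% v 20% | 5.0% | 2.5% | 0.4% | 0.0% |

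The step from Pearson to the correct Poisson is the cost of Poisson variance for a yes/no event. Only the step from the correct to the swapped Poisson belongs to this point: 61.5% to 45% or 1% in the first row.

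**The case against.** The strongest reply is that this is a slip of terminology and not a planned analysis. The sentence opens with the right aim, Poisson regression has one sensible form for that aim, and the groups are named only A and B, so a literal run would require inventing numeric codes. That is likely true. It makes it less probable that the wrong model will be run, but it does not make the text right.

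Several limits on the size also stand:
- The error affects one safety comparison. The primary outcome, the secondary outcomes and the sample size are unaffected, and the trial is not powered for AEs.
- If AEs are also tabulated as numbers and percentages, as the section provides for categorical variables, incidence by group will be visible whichever way the model is written.
- The fair comparator for the swapped P values is the correctly oriented Poisson (0.028), not the Pearson test (0.007 on the same counts), because part of the gap to Pearson comes from the Poisson variance.
- Between 0/1 and 1/0 coding the model-based P hardly moves (0.060 v 0.061). The large change needs 1/2 coding, which the article does not mention.
- A difference of 20% v 40% is large for two arms that share the same needle and basic points.

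None of this supplies a reading under which the stated model estimates AE incidence. Nor is it a detail left to a fuller document: the article chose to state the variable roles and stated them the wrong way round.

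**Conclusion.** The concern holds. As written, the model contradicts its own stated aim and cannot return the ratio of AE incidences. Where the assumed ratio is 2.00 it gives between 0.58 and 1.56, depending on an arbitrary coding, with P from 0.060 to 0.27 against 0.028 for the correct orientation. These sizes rest on assumed AE counts with 74 per group. The failure to recover the incidence ratio appeared for every set of counts tried. The consequence is confined to the safety comparison. The point should be corrected before analysis, and it gives no reason to doubt the rest of the design.

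**What to change.** Replace the second half of the sentence in Data analysis so that AE occurrence (participant with at least one AE, yes or no) is the dependent variable and treatment group is the independent variable, and carry the same wording into the analysis plan. That alone cures the error.

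Two additions are advisable while the sentence is open, though they are not part of the defect. First, report the group effect as a risk ratio or risk difference with a 95% confidence interval, with centre as a covariate in line with the primary model. Second, because the response is yes/no, use robust standard errors with the Poisson fit, or a log-binomial or exact comparison.

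Cost: one sentence in the protocol and the analysis plan, with no new data and no additional patients.

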## Discussion

This is the first study to evaluate the efficacy of acupuncture with intradermal needle for treating CSAP at different acupoint prescriptions. The results might deepen our knowledge on the theory of Meridian-Viscera Association and provide reference for the selections of acupoint prescriptions and acupuncture modality so as to develop better practice for acupuncture treating CSAP.

### The theory of Meridian-Viscera Association

As an important component of the acupuncture theoretic system, the Meridian-Viscera Association theory emphasizes the close relationship between meridians and viscera in physiological function, pathological changes, diagnosis, and treatment. In detail, viscera physiological functions and pathological changes will manifest in the corresponding meridians or the acupoints [25], and the viscera disorders can be treated with the involved meridian and acupoints [26]. That means gastric disorders can manifest on the Stomach Meridian and be treated with the acupoints on Stomach Meridian. Cardiovascular disease can reflect on the Heart/Pericardium Meridian and be treated with the acupoints on the Heart /Pericardium Meridian. A number of modern studies have confirmed the relatively specific relationship between meridians and viscera and the modulating effect of meridians/acupoints for the corresponding viscera functions [27, 28]. For example, our previous study found that puncturing at the acupoints on the Stomach Meridian can effectively improve the symptoms and QoL of the functional dyspepsia (FD) patients compared to puncturing at sham acupoints or the acupoints on the Gallbladder Meridian [29].

The CSAP pertains to heart-related diseases. Acupuncture treatment can be performed on the meridians/acupoints which is related to the heart. In light of the traditional Chinese acupuncture theory, the Heart Meridian is directly related to the heart, and the Lung Meridian is indirectly connected to the heart. The acupoints on these two meridians can all be used for cardiovascular diseases. Therefore, this study tries to compare the therapeutic effects of the acupoints on the Heart Meridian (direct-related meridian) and the acupoints on the Lung Meridian (indirect-related meridian) for treating CSAP.

### Acupoints selection

In clinical practice, selecting the local points and distal points simultaneously is the basic principle for developing acupoint prescriptions. In this study, the local acupoints, including *Xinshu* (BL15, the Back-shu point of the heart) on the back and *Juque* (CV14, the Front-mu point of the heart) on the chest, will be selected as the basic points because they are close to the heart and are the most commonly used local acupoints for cardiovascular diseases. For the distal acupoints, 3 acupoints on the Heart Meridian or on the Lung Meridian will be selected respectively as the additional acupoints. They all locate on the forearm, which is far from the heart. They are the *Shenmen* (HT7), *Yinxi* (HT6), and *Tongli* (HT5) on the Heart Meridian for group A and the *Taiyuan* (LU9), *Lieque* (LU7), and *Kongzui* (LU6) on the Lung Meridian will be selected respectively for group B. According to the literature analysis [16, 28], these 6 acupoints were all used for treating cardiovascular diseases. Among them, *Shenmen* (HT7) and *Taiyuan* (LU9) are the Yuan-source points of the Heart Meridian or the Lung Meridian, respectively; *Tongli* (HT5) and *Lieque* (LU7) are Luo-connecting points of the Heart Meridian or the Lung Meridian, respectively; and *Yinxi* (HT6) and *Kongzui* (LU6) are Xi-cleft points of the Heart Meridian or the Lung Meridian, respectively.

### Acupuncture modality selection

Intradermal needle is a kind of special acupuncture needle for superficial puncture, which could be inserted perpendicularly into the skin with a tiny needle and be fixed with a piece of adhesive tape for 1 to 3 days to produce a gentle continuous stimulation on acupoint [30]. Compared with the filiform needle, the intradermal needle has more convenient operation, less pain, and fewer adverse reactions [17, 18]. So the intradermal needle has recently been widely used for chronic diseases such as chronic tension-type headaches and insomnia [31, 32]. In addition, a small sample size clinical study also indicated that the intradermal needle could significantly improve the clinical symptoms of CSAP [33]. Therefore, considering the simplicity of the operation and the continuity of stimulation, the intradermal needle has been selected as the acupuncture modality in this study.

### Basic treatments with medicines

The guidelines from the Chinese Society of Cardiology and the American College of Cardiology/American Heart Association (ACC/AHA) hold that the basic treatment of CSAP mainly includes health education and primary drugs [21, 34]. So in this study, health education and medications are selected as the basic treatment for the patients with CSAP.

In this study, all patients are recommended to modify their lifestyles and control unhealthy habits that might affect diseases, such as limiting alcohol consumption, controlling weight, and quitting smoking. Health education is beneficial for the patients to be aware of the disease, to correct unhealthy behaviors and eating habits in daily life, and to avoid various accidents or adverse conditions during treatment and improve the safety of treatments.

Based on the guidelines [21, 34] and cardiologists’ recommendations, this study will select the four most commonly used medications as basic medications for treating CSAP, including β-blockers, ACEI, ARB, and antiplatelet medications and statins.

In conclusion, focuses on the theory of Meridian-Viscera Association, this study tries to investigate the efficacy differences in improving the symptoms of CSAP between two commonly used meridians (acupoints prescription), so as to provide evidence for the selections of acupoints and acupuncture modality. The results might be valuable for developing good practice for acupuncture treating CSAP.

